
### Intervention fidelity

To ensure the fidelity of the intervention, qualified therapists who have basic professional training in mindfulness-based intervention (e.g., a one-year foundation course of teaching mindfulness-based cognitive therapy as organized by the Oxford Mindfulness Centre and the Hong Kong Centre for Mindfulness) plus at least 2 years’ experience in conducting mindfulness-based programmes will be invited to implement the brief MBI. Through a two-day training programme, a team of qualified therapists will learn the rationale and contents of the brief MBI. They will also develop and practice skills in conducting the brief MBI. All intervention sessions will be audiotaped and assessed by another team of independent raters who are also qualified therapists. They will ensure the intervention’s fidelity by following the mindfulness-based interventions teaching assessment criteria scale [44] and the designed intervention protocol. For the qualitative part of the research, the research team will receive a one-day training course to learn the corresponding interview questions and the process for conducting the focus groups. In addition, regarding the qualitative analysis, another team of independent raters will audiotape, transcribe, and review the contents of the qualitative interviews to identify themes.

### Sampling

On the basis of the data from the pilot study results and according to the G*Power programme [45], and in order to achieve a statistical power of 0.8 with a medium effect size (f = 0.35) and a significance level of 0.05 in repeated measures, a multivariate analysis of variance under the proposed two-group, three-time-point design and a total sample size of 82 will be needed. Furthermore, for the path model analysis of the underlying mechanism with two latent variables and seven observed variables, a sample size of 138 is needed, according to an online calculator [46]. In addition, and as recommended by Kline [47], the minimum sample size to parameters ratio should be 10:1 in a path model. As there will be 10 potential parameters in the proposed model, the minimum sample size needed is 100. Thus, we will plan for a total of 138 participants. Assuming an attrition rate of about 10%, a final sample size of 154 (i.e., 77 per condition) will be enrolled into the study and randomized.

The inclusion criteria are as follows: (1) a diagnosis of Bipolar I or II disorder; (2) in a state of full remission for more than 2 months [48]; (3) no active suicidal ideation or self-harm behaviours; (4) on regular medication; and (5) aged 18 years old or above. People with a comorbid diagnosis of schizophrenia, schizoaffective disorder, substance misuse, organic brain syndrome, or intellectual disability will be excluded. A Structured Clinical Interview for DSM-IV Disorders (SCID; only the mood disorders sections) [49] will be administered by trained clinicians to confirm the diagnosis and remission status of the participants. Observation of mental state and any potential for self-harm behaviours will be closely monitored throughout the intervention and assessment processes. When necessary, participants will be advised to consult a professional. After completing the project, participants will be given cash coupons as incentives. Suitable participants will be recruited from various hospital-based and community-based psychiatric rehabilitation settings across Hong Kong. With an agreed partnership with a local non-governmental organization (NGO) and a collaborated hospital, initial permission has been sought for recruiting participants from these settings.

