### Pilot studies

A pilot quantitative study was conducted by the first author in mid-2018. Twenty people with BD were recruited in a randomized controlled trial; half of them were assigned to a brief MBI group, while the other half were assigned to a waiting list control group. Comparisons were made of the two groups. Participants in the brief MBI group showed significant improvement on the measured variables. Specifically, the primary outcome of personal recovery had a moderate effect size (d = 0.35). Interestingly, there was virtually no effect of treatment on the secondary outcome of functional recovery (d = 0.02). Other potential mediators also showed small to moderate effect sizes (d = 0.22 to 0.38). The results of this study are summarized in Table 1. The feedback collected from participants was used to refine the programme content.

**Table 1 Tab1:** Comparison of participants in brief MBI group and control group in a pilot study

Variable	Brief MBI group (*n* = 10)		Control group (n = 10)		Effect size
	Pre	Post	Pre	Post	
	Mean (sd)	Mean (sd)	Mean (sd)	Mean (sd)	Cohen’d
Independent variable (Mindfulness)					
FFMQ	117.4 (20.89)	122.3 (22.52)	116.7 (16.65)	114.9 (17.25)	0.37
Mediators (Emotion awareness and regulation)					
DERS	97.2 (22.68)	90.6 (19.89)	99.8 (17.43)	97.8 (18.07)	0.38
ERS	36.4 (24.78)	33.0 (22.83)	36.3 (12.95)	37.1 (13.0)	0.22
Mediators (Illness acceptance)					
ISMI	2.22 (.30)	2.1 (.34)	2.17 (.20)	2.18 (.19)	0.29
MDIS	11.15 (.97)	11.3 (.79)	11.2 (1.40)	11.0 (1.41)	0.26
Primary outcome (Personal recovery)					
BRQ	2327.5 (548.79)	2507.5 (504.43)	2322.5 (428.57)	2347.0 (394.73)	0.35
Secondary outcome (Functional recovery)					
FAST	27.3 (23.70)	26.6 (22.55)	27.3 (19.56)	27.1 (18.75)	0.02

*FFMQ* five facet mindfulness questionnaire, *DERS* difficulties in emotion regulation scale, *ERS* emotion reactivity scale, *ISMI* internalized stigma of mental illness, *MDIS* mood disorders insight scale, *BRQ* bipolar recovery questionnaire, *FAST* functional assessment short test

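### The sample size for Hypothesis 1 carries the pilot's d = 0.35 over as f = 0.35, so 80% power at N = 82 does not follow from the pilot effect, and power at 138 completers is left undetermined

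*Protocol article*

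**What the plan says.** Pilot studies section: "the primary outcome of personal recovery had a moderate effect size (d = 0.35"). Table 1 heads the column as Cohen's d and gives the post-intervention BRQ mean (SD) as "2507.5 (504.43") in the brief MBI group and "2347.0 (394.73") in the control group, 10 people in each.

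Sampling section: the calculation is introduced with "On the basis of the data from the pilot study results and according to the G*Power programme". The remaining inputs are "power of 0.8 with a medium effect size (f = 0.35"), "a significance level of 0.05 in repeated measures", and "a multivariate analysis of variance under the proposed two-group, three-time-point design". The result is a total of 82.

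The same section then takes 138 from a path-model calculator as the planning number and adds about 10% for attrition to reach 154 enrolled, 77 per arm. It gives no power for the BRQ at 138.

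The Data analysis section tests Hypothesis 1 with a repeated-measures factorial ANOVA and also fits a hierarchical linear model to the repeated measurements.

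**The concern.** The outcome, the number and the stated source are the same in the two sections; only the symbol changes from d to f. The two are on different scales. Cohen's d is a mean difference in SD units at one time point. The f of a repeated-measures interaction also depends on how strongly scores correlate within a person and on how the group difference develops over the three assessments. A pilot d therefore cannot be entered as f without stating both.

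The 82 is the only power statement in the article for the primary hypothesis. Set beside 138 planned completers it suggests a wide margin: at f = 0.35, power at 138 would be 0.96. If that margin is not real for the effect seen in the pilot, a null BRQ result could be read as coming from an amply powered trial when it did not.

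**Working it through.** **1. What the pilot's 0.35 is.** From the Table 1 post scores:

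- difference = 2507.5 − 2347.0 = 160.5
- pooled SD = √[(504.43² + 394.73²)/2] = 452.9
- d = 160.5/452.9 = 0.354

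The other six Table 1 effect sizes also reproduce as post-score differences over the pooled post SD. The 0.35 is thus a single-time-point d, not a repeated-measures f.

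**2. Reproducing the plan's 82.** For the repeated-measures MANOVA group-by-time interaction with 2 groups and 3 times: df1 = (2−1)(3−1) = 2, df2 = N − 3, noncentrality λ = f²N, alpha 0.05. With f = 0.35, f² = 0.1225:

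- N = 81: power 0.796
- N = 82: power 0.801

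The stated 82 is matched exactly, so the value entered was f = 0.35 and the arithmetic from that input is correct.

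**3. What f the pilot d implies in that test.** Assume compound symmetry with within-person correlation r, no group difference at T1, a difference d at T2, and a stated pattern at T3. Then f² = d²·S/[4(1−r)], where S is the sum of squared deviations of the pattern from its mean.

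- Effect sustained, pattern (0, 1, 1): S = 4/9 + 1/9 + 1/9 = 2/3, so f² = d²/[6(1−r)].
- Effect halved by T3, pattern (0, 1, 0.5): S = 0.25 + 0.25 + 0 = 0.5, so f² = d²/[8(1−r)].

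Setting f = d gives 6(1−r) = 1, r = 0.833, for the sustained effect, and 8(1−r) = 1, r = 0.875, for the halved effect. Below those correlations, d = 0.35 corresponds to an f smaller than 0.35.

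**4. Power at d = 0.35.** The article gives no correlation for this purpose, so r is an assumption shown over a range. The 0.866 is the four-week BRQ retest value quoted in the Measurements section.

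| r | Sustained: f | Power at 82 | Power at 138 | Halved by T3: f | Power at 138 |
|---|---|---|---|---|---|
| 0.5 | 0.202 | 0.343 | 0.546 | 0.175 | 0.428 |
| 0.7 | 0.261 | 0.535 | 0.780 | 0.226 | 0.648 |
| 0.8 | 0.320 | 0.721 | 0.924 | 0.277 | 0.829 |
| 0.866 | 0.390 | 0.884 | 0.987 | 0.338 | 0.950 |

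At r = 0.3 with a sustained effect, power at 138 is 0.41.

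**The case against.** The strongest reply has three parts.

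*The 82 may be right.* With a sustained effect and r near the quoted 0.866, 82 gives 88% power at d = 0.35. That stands as a possibility, and it rules out calling 82 an arithmetic error. But 0.866 is a four-week retest value, the follow-up here is at six months, and the Sampling section does not cite it as an input. The article states neither of the assumptions that would make 82 follow from the pilot.

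*The 82 does not set the sample size.* True: 138 comes from the path model. This limits the consequence, because no enrolment decision rests on 82. It does not supply a power figure for the BRQ at 138.

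*The substitution is inferred.* Also true. The shared value, the shared source and the exact reproduction of 82 make it the plain reading, but the article shows no working.

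A reader might go further and say that f = 0.35 means d = 0.70, twice the pilot effect, so that 318 people are needed and 138 give only 43% power. The documents do not support this as a general result. The rule f = d/2 belongs to a two-group comparison at a single time point. For the three-time interaction, the f = 0.175 behind those figures arises only under particular assumptions, for example r = 0.5 with the effect halving by T3. Nor must r reach 0.90 for the two metrics to agree; that value comes from a two-time change score, and about 0.83 suffices here with a sustained effect.

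**Conclusion.** The point holds as an unsupported power statement for the primary hypothesis. The pilot supplies d = 0.35, the calculation uses f = 0.35, and nothing in the article links the two. The claim of 80% power at 82 is met for the pilot effect only if the within-person correlation is about 0.83 or higher through six months with a sustained effect, or about 0.875 or higher if the effect halves. A flat statement that the trial is underpowered would go too far, because 138 completers reach 80% at r = 0.8 under either pattern and miss it at r = 0.7 under either. These figures rest on compound symmetry, no baseline difference, a true post-intervention d of 0.35 and the two time patterns shown. That d itself comes from 10 people per arm.

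**What to change.** In the Sampling section, remove f = 0.35 and 82 as the pilot-based requirement. In their place state:

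- the pilot effect as a between-group post-score d of 0.35 on the BRQ;
- the assumed within-person correlation across T1, T2 and T3, with its source;
- the assumed pattern of the effect at T2 and T3;
- the resulting power at 138 completers for the planned three-time group-by-time test, over a range of correlations such as the table above.

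Replacing f = 0.35 with f = 0.175 would not do, since that again applies a single-time conversion to a repeated-measures test. Nor would power for a baseline-adjusted T2 comparison, which the Data analysis section does not plan.

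The cost is one rewritten paragraph. Enrolment stays at 154 and no analysis changes. The only downside is that the stated power will be less favourable and will depend openly on the correlation.

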### Data analysis

The data will be analyzed using SPSS, version 24.0. The associations among different variables will be investigated using Pearson’s correlation analysis. To test Hypothesis 1, a factorial ANOVA with repeated measures will be conducted. Hierarchical linear modelling (HLM) will be employed to test the individual growth model by studying repeatedly measured data. This integrated random-coefficients approach is usually conceptualized as a two-level model. Level 1, or the within-subject model, is the model for repeated measures with time-varying variables nested within individuals, whereas level 2, or the between-subject model, is the model for time-invariant variables between groups of individuals. SPSS mixed will be used in performing the HLM. In order to reduce the possible effects of multicollinearity, grand mean centring of different plausible predictors will be done before further data analysis. The fit of the models will be assessed and compared using appropriate fit statistics, including likelihood ratio tests and Akaike information criterion correction [50].

To test Hypotheses 2 and 3, the macro PROCESS SPSS and the bootstrapping approach [51] will be used to assess the moderated mediation effects in the path model. Each predictor will be mean centred to form the interaction terms. The effects of covariates such as age or gender will be adjusted accordingly. The PROCESS macro is based on ordinary least squares regression. In all analyses, the significance level will be set to *p* < 0.05.

To test Hypothesis 4, the contents of the focus group interview will be audiotaped and transcribed by a team of independent raters. Thematic analysis will be conducted with the help of the software NVivo (version 10.1.3) for storing and managing the data. The coding and analysis will use interpretative phenomenological analysis (IPA [52];). The IPA will allow a bottom-up approach to determine the themes. Throughout the analysis, the codes will be identified from frequently used words or ideas from the transcripts. Codes will then be categorized into larger recurrent themes for further analysis. The combined analysis of the Photovoice pieces and corresponding narratives will use the iconographic and thematic analyses approaches [53]. The research team will meet to discuss the significance of each theme and triangulate the results with the quantitative findings.

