### Measurements

The psychometric attributes of all the measurement tools used in this project, such as reliability and validity, are psychometrically sound. For those assessments without a Chinese version, translation and cultural adaptation have been made with reference to the guidelines for the translation and adaptation of psychometric scales [36]. Outcome assessment will take place at baseline (T1), after intervention (T2), and at a six-month follow-up (T3). All participants will be assessed in terms of the following:

Primary outcome:

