➢ Personal experiences of BD recovery: This will be assessed using the Bipolar Recovery Questionnaire (BRQ; 37). This 36-item questionnaire measures an individual’s experiences of recovery, such as personal understanding of self, sense of personal agency, or identifying recovery as a dynamic process. Total score is calculated by summing individual scores across all items. Evidence supports the internal consistency of the total score (*α* = .875) and good test-retest reliability over 4 weeks (*r* = .866) [37]. A higher total score indicates better personal recovery.Mediators:➢ Emotion awareness and emotion regulation: These will be assessed using the Chinese version of the Difficulties in Emotion Regulation Scale (DERS [38];) and the Emotion Reactivity Scale (ERS [39];). The DERS is a 36-item questionnaire that measures adults’ difficulties in emotion regulation. Evidence supports the scale’s internal consistency (*α* = .9) and good test-retest reliability over 2 weeks (*r* = .84) [38]. A higher total score suggests greater problems with emotional regulation. The ERS is a 21-item self-report measure of emotion sensitivity, intensity and persistence. Evidence demonstrates the good consistency (*α* = .94) of the scale [39]. A higher total score indicates greater emotional reactivity.➢ Illness acceptance: This will be assessed by the Internalized Stigma of Mental Illness Scale (ISMI [40];) and the Mood Disorders Insight Scale (MDIS [41];). The ISMI is a 9-item short form that measures self-stigma. Evidence supports the good consistency of the scale (*α* = .86) [40]. A higher total score reflects higher levels of reported internalized stigma. The MDIS is an 8-item scale that measures insight of mood disorders. Evidence supports the scale’s satisfactory test-retest reliability over 1 week (*r* = .75). Validity testing of the scale was based mainly on clinician ratings (r = 0.49) [41]. A higher total score indicates greater insight.Moderator:➢ BD stage will be operationalized as the number of previous BD episodes [6, 25]. Consistent with previous prospective studies on BD stage [13, 42], the number of previous episodes will be categorized as less than 5, 5 to 10, and more than 10.Independent variable:➢ Mindfulness: This will be assessed by the Chinese version of the Five Facet Mindfulness Questionnaire (FFMQ [43];). The FFMQ is a 39-item questionnaire which consists of five subscales: Observing, Describing, Acting with Awareness, Non-judging of Inner Experience, and Non-reactivity to Inner Experience. The five factors form a total mindfulness score which reflects a global measure of mindfulness. Evidence supports the scale’s good consistency (*α* = .83) and test-retest reliability over 2 weeks (*r* = .88) [43]. A higher total score indicates greater levels of mindfulness.

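### The Hypothesis 1 ANOVA treats the pre-treatment BRQ as an outcome level; adjusting for it instead would be valid, free and at least as powerful, with a gain that depends on a correlation the protocol does not give

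*Protocol article*

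**What the plan says.** The Data analysis section names the test for the primary outcome: "To test Hypothesis 1, a factorial ANOVA with repeated measures will be conducted". It then adds a second model: "Hierarchical linear modelling (HLM) will be employed to test the individual growth model by studying repeatedly measured data". That model is to be run in SPSS MIXED, and no fixed effects are listed for it. The only covariates named anywhere, age and gender, are in the paragraph on Hypotheses 2 and 3.

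The Measurements section puts the BRQ at T1 (baseline), T2 (after the intervention) and T3 (six months). The Sampling section sizes the Hypothesis 1 test "in order to achieve a statistical power of 0.8 with a medium effect size (f = 0.35) and a significance level of 0.05 in repeated measures", as "a multivariate analysis of variance under the proposed two-group, three-time-point design and a total sample size of 82 will be needed". There are three time points only if T1 is counted as an outcome level.

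The larger path-model requirement sets the final number: "Thus, we will plan for a total of 138 participants", with 154 enrolled to allow for attrition. The only BRQ correlation over time is in the Measurements section, which reports "good test-retest reliability over 4 weeks" with r = .866.

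**The concern.** T1 is measured before any treatment. Randomisation makes the expected T1 difference between arms zero. A group-by-time interaction that includes T1 nevertheless estimates that difference and subtracts all of it from each follow-up difference. This has two consequences:

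- **Noise.** Sampling error in the T1 difference is carried into the treatment contrast.
- **Over-correction.** The interaction removes the whole of a chance T1 imbalance, whereas regression on T1 removes only rho times it. The excess is (1 − rho) times the imbalance.

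What is at stake is power and precision on the primary hypothesis. The T1 BRQ is already scheduled for all participants, so the lost precision saves nothing.

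**Working it through.** **1. Inputs.** From Sampling: f = 0.35, alpha 0.05, power 0.80, N = 82 for this test, 138 completers, 154 enrolled in equal arms. From Pilot studies: BRQ d = 0.35; Table 1 confirms this is on the raw post-treatment SD scale, since (2507.5 − 2347.0) / √[(504.43² + 394.73²)/2] = 0.354. From Measurements: BRQ test-retest r = .866 over 4 weeks. No six-month correlation is given, so rho is an assumption, taken from 0.5 to .866.

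**2. Reproducing the plan's figure.** For a 2-df group-by-time test with three levels, lambda = N f² on F(2, N − 3).
- N = 82: lambda = 82 × 0.1225 = 10.05, power 0.8015.
- N = 81: power 0.796.

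So 82 is the first N to reach 80%. Three other G*Power-type readings were tried (between-groups factor, univariate interaction, and multivariate interaction with rho 0.5). They give 45, 15 and 17. The stated figure therefore confirms that the sized test is the interaction with T1 as one of the levels. The attrition step also reproduces: 138 / 0.9 = 153.3, rounded up to 154.

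**3. Variance at a single follow-up visit** (unit SD).
- Change from T1: 2(1 − rho).
- Adjusted for T1: 1 − rho².
- Ratio: 2/(1 + rho), which is 1.33 at rho 0.5, 1.18 at 0.7 and 1.07 at .866.

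**4. The 2-df test, equal correlations.** Unadjusted lambda is (N/4) δ′(CSC′)⁻¹δ, where C forms T2 − T1 and T3 − T1 and S is the correlation matrix. Adjusted lambda uses the covariance of (T2, T3) given T1. The ratio of adjusted to unadjusted is:
- effect equal at T2 and T3: 3/(1 + 2rho);
- effect at T2 only: 1.5(1 + rho)/(1 + 2rho).

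**5. Power at N = 138, d = 0.35, two-sided 5%** (unadjusted to adjusted).

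| rho | 2-df, effect sustained | 2-df, effect at T2 only | T3 alone, 1 df |
|---|---|---|---|
| 0.5 | 54.6% to 73.2% | 54.6% to 59.9% | 53% to 65% |
| 0.6 | 65% to 79% | 65% to 69% | 63% to 72% |
| 0.7 | 78.0% to 86.8% | 78.0% to 80.5% | 75% to 82% |
| .866 | 98.7% to 99.3% | 98.7% to 98.9% | 97.6% to 98.3% |

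With half the effect left at T3, the 2-df gain is about 13, 11, 8 and 1 points at rho 0.5, 0.6, 0.7 and .866.

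**6. The plan's own f = 0.35 at N = 138.** Unadjusted lambda = 138 × 0.1225 = 16.9, power 96.2%. Multiplying lambda by 3/(1 + 2rho) gives 99.6% at rho 0.5, 98.8% at 0.7 and 97.5% at .866. The gain is 1.3 to 3.4 points.

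**The case against.** The strongest reply is that this is a conventional analysis, consistent with its own sample size, and that the loss may be trivial. Much of that stands.

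- **It is not an error.** A reader might infer that the interaction test is biased or invalid. It is not: randomisation protects it, and the design was sized for the same test.
- **The loss may be negligible.** T2 follows four weekly sessions, close to the 4-week interval behind r = .866. At that value the gain at 138 completers is about one power point or less. If T1–T2 stays at .866 and only the T3 correlations fall to 0.5, the 2-df gain for a sustained d = 0.35 is about 2 points (96% to 98%).
- **N = 82 is not the trial.** A reader might take the sizing case, where adjustment lifts 80% to 94% at rho 0.5, as the power given up. But 82 is only the smallest of the listed requirements, and 138 completers are planned. At that number and the plan's f, the gain is 3.4 points at most.
- **The mixed model is not pinned down.** A reader might assume that the SPSS MIXED growth model also lets the arms differ freely at T1. The article lists no fixed effects for it, so a T1 term or a common T1 mean is unstated, not excluded. That detail may properly sit in an analysis plan that is not shown.

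The reply does not rescue the ANOVA. It is the method named for Hypothesis 1, its three levels include T1, and nothing in the text adjusts for T1. Four-week stability without treatment also does not establish the correlation over six months that span an intervention meant to change the BRQ.

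**Conclusion.** The point holds as an efficiency improvement to the stated Hypothesis 1 ANOVA. The planned test is valid. Apart from one degree of freedom, adjusting for T1 is never worse for rho below 1.

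At 138 completers and the pilot d = 0.35, the gain is material (about 7 to 19 points) if the correlations are 0.5 to 0.7 and either the effect is fully sustained or the six-month comparison is taken alone. It is about 5 points or less if the effect is confined to T2, at most 3.4 points at the plan's f = 0.35, and around one point or less at rho = .866.

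These figures assume equal variances, equal correlations across visits and complete data on 138 participants. The main unknown is the six-month correlation, which the article does not give, so no single figure for the loss can be stated.

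**What to change.** In the Data analysis section, replace the Hypothesis 1 test with a statement along these lines: Hypothesis 1 will be tested in SPSS MIXED with the T2 and T3 BRQ as outcomes; fixed effects for arm, visit, arm-by-visit, T1 BRQ and T1 BRQ-by-visit; and an unstructured within-person covariance. An equivalent choice is to keep T1 as an outcome but hold the two arms to a common T1 mean. Report the arm difference from this model in place of the ANOVA group-by-time F test.

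The cost is one sentence. The T1 BRQ is already collected from all participants and SPSS MIXED is already planned, so no patients, visits or software are added. The sample size can stay as it is, because the path-model requirement of 138 sets it.

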## Methods/design

### Aims of the research project

Here, we propose a research programme that addresses all of the aforementioned knowledge gaps, including research that will enable us to understand the psychological mechanisms underlying recovery [7]. Specifically, the aims of the research project are as follows:
To examine the effectiveness of a brief MBI for enhancing personal recovery in a sample of individuals with BD relative to a waiting list control condition.To evaluate the mediating roles of emotion awareness, emotion regulation, and illness acceptance as mechanisms underlying the beneficial effects of the brief MBI.To investigate the moderating role of BD stage on the beneficial effects of the brief MBI.To better understand the participants’ lived experience of mindfulness in relation to the personal recovery process.

On the basis of the conceptual model depicted in Fig. 1, we will address these aims by testing the following specific hypotheses:
The brief MBI will be more effective, with a higher effect size, than the waiting list control on measure of the primary outcome of personal recovery.The beneficial effects of the brief MBI on measure of personal recovery will be mediated by treatment-related increases in emotion awareness, emotion regulation, and illness acceptance.The hypothesized mediation effects will be moderated by BD stage: that is, individuals with BD who report having a lower number of previous BD episodes will evidence stronger mediation effects for treatment-related changes in emotion awareness and emotion regulation, whereas individuals with BD who report having a higher number of previous BD episodes will evidence stronger mediation effects regarding illness acceptance.The qualitative analysis will increase our understanding of the effects and mechanisms of the brief MBI interventions.

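### Hypothesis 1 is tested by a repeated-measures ANOVA with no deciding term or time point and an unranked growth model beside it, although the software for a better mixed model is already planned

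*Protocol article*

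**What the plan says.** All references are to the protocol article.

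- **Aims of the research project.** Hypothesis 1 reads: "The brief MBI will be more effective, with a higher effect size, than the waiting list control on measure of the primary outcome of personal" recovery. It names no visit and no contrast.
- **Measurements.** The Bipolar Recovery Questionnaire (BRQ) is the primary outcome. "Outcome assessment will take place at baseline (T1), after intervention (T2), and at a six-month follow-up (T3").
- **Data analysis.** "To test Hypothesis 1, a factorial ANOVA with repeated measures will be conducted". The next sentence adds a second longitudinal model: "Hierarchical linear modelling (HLM) will be employed to test the individual growth model by studying repeatedly measured data". That sentence cites no numbered hypothesis. "SPSS mixed will be used in performing the HLM", with models compared by likelihood ratio tests and an Akaike-type criterion. "In all analyses, the significance level will be set to *p* < 0.05".
- **Sampling.** The group comparison is sized on a third form, a repeated-measures MANOVA with two groups and three time points (f = 0.35, power 0.8, total 82). The path model raises the target to 138. "Assuming an attrition rate of about 10" per cent, 154 are randomised, 77 per condition.

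**The concern.** A two-group, three-visit ANOVA yields a group main effect and a group-by-time interaction, and the article does not say which one answers Hypothesis 1. The main effect averages in the pre-treatment score. The interaction is an omnibus test that rejects for any departure from parallel profiles, so a lasting benefit and one that has vanished by six months look alike to it. The growth model offers a further p-value at the same level with no rank. With several candidate outputs, the reading of the primary outcome could be chosen after the results are known.

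The named test is also the one that, in its usual software form, loses participants with a missed visit. The model that keeps them is already planned for another purpose.

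**Working it through.** **Inputs from the article:** f = 0.35, power 0.8, alpha 0.05, N = 82; 138 analysable and 154 randomised; pilot d = 0.35 on the BRQ after intervention (Table 1); four-week BRQ retest correlation 0.866 (Measurements).

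**Assumptions, not in the article:** compound symmetry; correlation between visits 0.5, 0.7 or 0.866; two-sided tests; a T2 effect of 0.35 SD; the T3 patterns below. The 0.35 SD is the pilot d. Whether the plan's f = 0.35 translates it properly is a separate question.

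**1. The plan's own figures.** For the MANOVA group-by-time interaction, λ = f²N = 0.1225 × 82 = 10.045, with 2 and N − 3 = 79 df. Power is 0.8015, and N = 81 gives 0.796, so 82 reproduces. Of the other forms tried, the ANOVA between-group term needs 24 to 61 and the ANOVA interaction 6 to 28 (correlation 0 to 0.866). Attrition: 138/0.9 = 153.3, rounded up to 154, also reproduces.

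**2. Who enters the ANOVA.** 154 × 0.9 = 138.6, so about 138 participants if everyone with a missed visit is dropped.

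**3. What the interaction can tell.** Arm differences at T1, T2, T3 are (0, 0.35, 0.35) if sustained and (0, 0.35, 0) if faded. The sum of squared deviations from the mean is (2/3) × 0.35² = 0.0817 for both. With 69 per arm, λ = (69/2) × 0.0817/(1 − ρ), with 2 and 135 df. Power is therefore identical for the two patterns.

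**4. Baseline-adjusted T2 contrast, same 69 per arm.** The standardised effect is 0.35/√(1 − ρ²), multiplied by √(69/2) = 5.874 for the noncentrality, with 135 df.

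| ρ | Interaction λ | Interaction power | Adjusted T2 noncentrality | Adjusted T2 power |
|---|---|---|---|---|
| 0.5 | 5.64 | 55% | 2.37 | 65% |
| 0.7 | 9.39 | 78% | 2.88 | 82% |
| 0.866 | 21.03 | 98.7% | 4.11 | 98.3% |

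For comparison, the group main effect has effect (0 + 0.35 + 0.35)/3 = 0.233 and variance (1 + 2ρ)/3. Its power is 38% at ρ = 0.5 and 33% at 0.7.

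**5. ANOVA against growth slope.** In simulation (77 per arm, 10% dropout, ρ 0.5 or 0.7, linear time coded 0/1/2 or 0/1/7 months), the interaction and the group-by-time slope differed on significance in these shares of trials:

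- sustained effect: 14–37%
- halved by T3: 31–61%
- gone by T3: 43–77%
- growing: 13–15%
- no effect: about 5%

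For the faded effect at ρ = 0.7, the ANOVA rejected in about 79–81% of trials and the slope in about 4–22%.

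Analytically, with times 0, 1, 7 the sum of squares is 28.67. The slope differences are 0.0326 (sustained), 0.0061 (halved) and −0.0203 (faded) SD per month. Over ρ 0.5 to 0.866, power in the beneficial direction is 30–79% if sustained and about 5–8% if halved.

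**6. Dropout bias.** Simulation with true T3 effect 0.35 SD, ρ = 0.7, and brief MBI participants with poor T1–T2 change dropping out more often:

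| Attrition | Completers only | Likelihood, all available data |
|---|---|---|
| 10% | 0.38–0.40 | about 0.35 |
| 20% | 0.41–0.44 | about 0.35 |
| 30% | 0.45–0.47 | about 0.35 |

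When dropout was unrelated to outcome, neither estimate was biased.

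**The case against.** The strongest reply is that Hypothesis 1 does have a named test. The ANOVA is tied to it explicitly, while the growth model has its own stated purpose. The sizing points to the interaction, which is the customary treatment test in this design. This largely stands: the ANOVA is the named test and the hierarchical model is merely unranked. It does not supply the missing piece, because the analysis section never names the interaction, and even a named 2-df interaction gives neither time nor direction. The low power of the main effect should carry little weight, since the plan does not size on that term.

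Two stronger readings are tempting, and the article does not support them.

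- **That the plan prescribes a complete-case analysis and discards dropouts.** It never says so. This is inferred from how classical repeated-measures ANOVA behaves in SPSS, and SPSS MIXED keeps incomplete cases. Missing-data rules may stand in an analysis plan not shown, so their absence is not held against the article.
- **That the two models will give opposite answers.** Differing significance is what the check supports in general. A slope that significantly favours the waiting list (14–41% of trials over ρ 0.5 to 0.866) needs linear time, 0/1/7-month coding and a fully faded effect together. The article states none of these; time could be categorical or piecewise.

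It is also fair to say that a repeated-measures ANOVA is a valid test of a group-by-time effect, and that its power disadvantage disappears at high correlation.

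**Conclusion.** The point holds in limited form. The article fixes a test for the primary hypothesis without fixing which term or visit decides it, and sets a second model beside it without rank. The term implied by the sample size cannot distinguish a lasting effect from a lost one.

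The power gain from a baseline-adjusted T2 contrast is about 10 percentage points at correlation 0.5, about 4 at 0.7 and none at 0.866. The six-month correlation is unknown. The gain in freedom from bias is up to about 0.05 SD at 10% attrition, only if dropout relates to outcome, and up to about 0.12 SD at 30%. If time in the growth model were linear, a T2 benefit that fades by T3 would largely be missed; that coding is an assumption.

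The main reason to act is that the answer on the primary outcome should not depend on which output is read.

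**What to change.** Make one likelihood-based mixed model in SPSS MIXED the test of Hypothesis 1:

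- all randomised participants, in their assigned arm;
- BRQ at T2 and T3 as outcomes, with baseline BRQ as covariate;
- time as a category, arm, and arm-by-time;
- unstructured covariance;
- fixed in advance, not selected by fit statistics.

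Name one primary contrast: the arm difference at T2, where the pilot d was measured, or at T3. That choice is the investigators'. The other becomes secondary. Label the ANOVA and the growth model as supportive, and state how the growth model codes time.

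The cost is wording: the software and assessments are already planned. The one real downside is that the claim at the other time point becomes secondary. A participant with no score after baseline still adds nothing to this model, and its protection against bias assumes that dropout is explained by observed scores.
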